### Adverse events

All unexpected adverse events related to CKJ intake will be reported to the investigator by subjects and write on the individual case report form by the investigator. Safety will be assessed by the reporting of clinical laboratory tests, vital sign measurements, and adverse events. Clinical laboratory tests, including blood test (white blood cell [WBC], red blood cell [RBC], hemoglobin, hematocrit, platelets count, total bilirubin [TB], alkaline phosphatase [ALP], alanine transaminase [ALT], aspartate aminotransferase [AST], total protein, albumin, blood urea nitrogen [BUN], creatinine, creatine kinase [CK]), and urine test (specific gravity, pH, nitrite, protein, glucose, ketone, urobilinogen, bilirubin, microscopic RBC/WBC) will be determined at weeks 0 (baseline) and 12 (end of the trial). Vital signs of each subject will be checked with monitoring of AEs (any AEs related to CKJ intake) after each visit.

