### Randomization and allocation concealment

After enrollment, subjects will be randomly assigned to one of the two groups, either the CKJ group or placebo group. The allocation ratio will be 1:1 in blocks of 2. Randomization will be performed at a site remote from trial location. Random numbers will be generated by a computerized random-number generator through the block-randomization method of a software program (Excel, Microsoft Office 2007) for sequence generation. At the time of randomization subjects will draw an envelope. Each envelope contains a number that is concealed to the treatment allocation. Randomization sequence and allocation will be concealed to all study subjects, research staff, investigators and pharmacists until completion of the study. The allocation list will be protected by password access files and held by a non-investigator independent. In the event of an emergency medical situation the individual’s randomization code and group allocation can be identify.

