	** *Crossover design* **				
	** *Screening* **	** *Baseline* **			** *Follow up* **
	** *Visit 1* **	** *Visit 2, 5* **	** *Visit 3, 6* **	** *Visit 4, 7* **	** *(Visit 8)* **
	** *D-28* **	** *Week 0* **	** *Week 6* **	** *Week 12* **	** *Week 24* **
	** *~D-1* **	** *D0* **	** *D42* **	** *D84* **	** *D168* **
** *Informed consent form* **	◯				
** *Demographic information taking* **^ ** *1* ** ^	◯				
** *Medical history taking* **	◯				
** *Inclusion/exclusion criteria check* **	◯	◯			
** *Physician examination* **^ ** *2* ** ^		◯		◯	◯
** *Drinking/smoking taking status* **^ ** *3* ** ^		◯		◯	
** *Vital sign measurement* **	◯	◯	◯	◯	◯
** *Concomitant drugs check* **	◯	◯	◯	◯	◯
** *Anthropometric measures* **^ ** *4* ** ^		◯	◯	◯	◯
** *Glucose parameter* **^ ** *5* ** ^		◯		◯	
** *Lipid profile* **^ ** *6* ** ^		◯		◯	
** *Adipocytokine* **^ ** *7* ** ^		◯		◯	
** *Carnitine assay* **		◯		◯	
** *Laboratory test* **^ ** *8* ** ^		◯		◯	
** *Study product distribution* **		◯	◯		
** *Compliance checking* **			◯	◯	
** *Adverse event monitoring* **		◯	◯	◯	◯
** *Diet, physical exercisecounseling* **^ ** *9* ** ^		◯	◯	◯	◯

◯: Item need to be performed during the visit.

^1^ Sex, date of birth, age, contact address and phone number.

^2^ Include present illness, past history taking.

^3,9^Risk factors such as alcohol drinking, smoking, severe exercise and other dietary supplement intake will be managed.

^4^ weight, body mass index, body fat mass, percentage body fat, lean body mass, waist circumference, hip circumference, and waist to hip ratio.

^5^ fasting glucose, HbA1c, insulin, gamma-glutamyl transferase (GGT).

^6^ total cholesterol, triglycerides, high-density lipoprotein-cholesterol (HDL-C), low-density lipoprotein-cholesterol (LDL-C), free fatty acid, apolipoprotein A1 (Apo A1), apolipoprotein B (Apo B), high-sensitivity C-reactive protein (hs-CRP).

^7^ leptin, adiponectin, ghrelin.

^8^ Blood test (white blood cell [WBC], red blood cell [RBC], hemoglobin, hematocrit, platelets count, total bilirubin [TB], alkaline phosphatase [ALP], alanine transaminase [ALT], aspartate aminotransferase [AST], total protein, albumin, blood urea nitrogen [BUN], creatinine, creatine kinase [CK]), urine test (specific gravity, pH, nitrite, protein, glucose, ketone, urobilinogen, bilirubin, microscopic RBC/WBC).

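### The adverse-event recording rule is limited to events related to CKJ (in one sentence, only unexpected ones), conflicts with the article's other safety wording, and cannot be applied reliably under blinding

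*Protocol article*

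**What the plan says.** The Adverse events section of the Protocol article describes adverse-event collection in three ways.

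- **What is written down:** "All unexpected adverse events related to CKJ intake will be reported to the investigator by subjects", and the investigator then enters them on the case report form. This is the only sentence that says what reaches the form.
- **What is monitored at visits:** "monitoring of AEs (any AEs related to CKJ intake) after each visit".
- **What safety rests on:** "Safety will be assessed by the reporting of clinical laboratory tests, vital sign measurements, and adverse events". Here adverse events carry no qualifier.

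Table 1 has a row headed "Adverse event monitoring", also without a qualifier. It is marked for the baseline visits (2 and 5), the week 6 visits (3 and 6), the week 12 visits (4 and 7) and the follow-up visit (8).

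The section on randomization and concealment says that "allocation will be concealed to all study subjects, research staff, investigators and pharmacists until completion of the study".

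**The concern.** A placebo-controlled comparison of adverse events needs the same events counted in the same way on both products. Here the recording rule asks, before an event is counted, whether it is related to the active product. The people asked are masked to which product is being taken. In one of the two sentences the event must also be unexpected.

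Two things are at stake. Events may go unrecorded, and they cannot be recovered at analysis. A real excess on CKJ that nobody attributes to the product at the time could then be missed. And if the judgement is made more readily in one product period than in the other, the recorded difference is distorted. The article presents this trial as groundwork for a larger one on efficacy and safety, so a gap here would carry forward.

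**Working it through.** **Comparison of the text**

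| Place in the article | Limited to CKJ-related? | Limited to unexpected? | Placebo mentioned? |
|---|---|---|---|
| Adverse events: what is written on the form | yes | yes | no |
| Adverse events: visit monitoring | yes | no (any event) | no |
| Adverse events: components of safety | no | no | no |
| Table 1: monitoring row | no | no | no; covers both periods |

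1. The relatedness limit stands in both specific sentences, so it is unlikely to be a slip. The expectedness limit stands in one and is contradicted by the other.
2. Table 1 says when to ask; the Adverse events section says what to write down. The table contradicts the rule but does not replace it.
3. Relatedness to CKJ presupposes that CKJ was taken. Under the stated concealment, neither subject nor investigator knows this when the event is recorded. The most they can judge is relatedness to a masked product, which is not what the rule says.
4. Laboratory tests "will be determined at weeks 0 (baseline) and 12 (end of the trial", and vital signs are measured at every visit. Neither carries a causality filter.

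**Size, on assumed rates**

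The article gives no adverse-event rate and no safety power, so there is no figure to reproduce. The following is an illustration only. From the article: 60 subjects per group (120 in total, 1:1), taken as the first period without dropout. Assumed: the true risks on CKJ and placebo, and the share of events that pass the filter in each arm. The two-sided level is 0.05.

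Recorded risk = true risk × share kept, written a for CKJ and b for placebo. With p̄ = (a + b)/2,

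power = Φ{ [ (a − b) − 1.96·√(2p̄(1 − p̄)/n) ] / √([a(1 − a) + b(1 − b)]/n) }.

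Example: true risks 30% and 10%, half kept in each arm. Then a = 0.15, b = 0.05, p̄ = 0.10. The numerator is 0.10 − 1.96 × 0.0548 = −0.0074, the denominator is 0.0540, and power = Φ(−0.136) = 0.446.

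| True risk, CKJ / placebo | Share kept, CKJ / placebo | Recorded difference | Chance of declaring an excess on CKJ |
|---|---|---|---|
| 30% / 10% | all / all | 20 points | 79% |
| 30% / 10% | 50% / 50% | 10 points | 45% |
| 30% / 10% | 25% / 25% | 5 points | 24% |
| 40% / 20% | all / all | 20 points | 67% |
| 40% / 20% | 50% / 50% | 10 points | 33% |
| 40% / 20% | 25% / 25% | 5 points | 18% |
| 20% / 20% | 50% / 50% | 0 | 2.5% (nominal, one tail) |
| 20% / 20% | 50% / 10% | 8 points, spurious | 45% |
| 20% / 20% | 50% / almost none | 10 points, spurious | 72% |

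The last two rows rest on very few recorded placebo events (60 × 0.02 = 1.2, and about 0), where the normal approximation is rough. Counting 120 exposures per product as if independent raises all power figures but keeps the pattern: for 30% and 10%, power goes from 98% to 74% with half kept and 43% with a quarter kept.

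The rows show two separate effects. Equal filtering shrinks a true difference and costs power, but creates no difference where there is none. Only unequal filtering creates a false one.

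**The case against.** A reader might infer that expected events never reach the form, that placebo events are excluded by definition, and that the safety comparison as a whole is invalid. The documents do not support that reading.

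- The article nowhere says that other events are excluded. It speaks of adverse events without a filter in the same section and in Table 1. The expectedness limit is contradicted by the visit-monitoring sentence.
- Blinding works against the idea that placebo events drop out by definition. A masked recorder can attribute a placebo-period event to the product as readily as a CKJ-period event. If so, the filter is equal and produces no false signal. The placebo is described as matched in taste and appearance, and nothing in the article shows that masking fails.
- Laboratory tests and vital signs are collected on everyone, whatever the suspected cause.
- Safety is not among the listed objectives, and the Discussion leaves confirmatory conclusions on efficacy and safety to a full-scale trial.
- Form fields, grading and table layouts properly belong to the full protocol or analysis plan, and their absence from an article is no fault.

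All of this stands, and it limits the point to the adverse-event data. It does not remove it. The article is not silent on recording. It states a restrictive rule that its own other wording contradicts and that blinded staff cannot apply as worded. Equal filtering still loses events and power.

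**Conclusion.** The point holds in limited form. The adverse-event wording is inconsistent within its own section and with Table 1, and the specific rule rests on a judgement that blinding makes impossible at the time of recording. Applied as written, it under-records adverse events and weakens the comparison between products. It opens that comparison to bias only if events are filtered unequally, which is possible but not shown.

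The size depends on assumed event rates and assumed shares kept. In the first-period illustration, keeping between half and a quarter of events in both arms takes power for a 20-point excess from 67–79% down to 18–45%. The textual contradiction needs no assumption. The laboratory and vital-sign parts of the safety assessment are untouched. The wording should be corrected.

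**What to change.** Reword the Adverse events section to agree with Table 1. All adverse events in both product periods, in washout and in follow-up should be recorded on the case report form, whatever their expectedness or suspected cause. Relatedness should be judged separately, by blinded staff, and to the study product rather than to CKJ. Adverse events should then be compared by the product taken. Delete the limits to unexpected and to CKJ-related events from the recording and monitoring sentences.

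The cost is a change of wording and slightly more form entry. No visit is added: monitoring is already scheduled at Visits 2 to 8, with Visit 5 following the washout and Visit 8 serving as follow-up. Detailed form fields and table layouts can stay in the full protocol and analysis plan.

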### Participant protection and ethics

The study protocol and the written informed consent were approved by the Functional Foods Institutional Review Board of Chonbuk National University Hospital (CUH IRB 2013-01-002). Each subject will be notified regarding the study protocol. Written informed consent will be obtained from each subject.

## Discussion

The aim of this study is to evaluate the efficacy of the CKJ on the Met-S. For this purpose, the ability of the CKJ to variables the Met-S will be assessed in 120 overweight/obese subjects.

In this study, we expect that the CKJ effectively reduction of risk factor for Met-S. Some studies have investigated the action of CKJ on the Met-S. The clinical trial for Met-S enhancement of CKJ has not been performed up to this time. However, numerous studies have reported from in vivo and in vitro studies [10-19]. Therefore, if this study will be successfully performed, the CKJ may offer beneficial effects in reducing of risk factor for Met-S. And these results will have important implications for the design of sustainable cost-effective health services for people with Met-S caused by obesity. In addition, this study will be the groundwork for the larger scale RCT. To draw confirmative conclusion about the therapeutic efficacy and safety of the CKJ, a full-scale RCT will be performed.
